### Sample size calculation

Sample size was projected with change in VO_2_max as the main outcome variable. The means and standard deviations of a previous study [5] were examined and the effect size for this research study was calculated. Assuming a power of 0.80 was needed and the calculated effect size for change in VO_2_max was 0.30, it was determined that approximately 16 participants would be needed for each group [12]. It is assumed there would be an approximate 20% dropout rate, so the aim will be to achieve 20 participants per group.

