### Intervention

#### Testing

Testing sessions for both the experimental and control groups will be conducted at baseline and every fourth week during the 12-week intervention period. Testing sessions every fourth week will help to establish the current physiological levels to develop the exercise prescription for the experimental groups.

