### Statistical analysis

All analyses will be performed using IBM SPSS Version 22.0 (Armonk, NY, USA) and GraphPad Prism 6.0 (GraphPad Software, San Diego, CA, USA).

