#### Time course changes

Measures of centrality and spread will be presented as mean ± standard deviation (SD) and ranges will be reported for each measure. The precision of estimates will be reported as 90% confidence limits. Baseline-dependent variables will be compared using general linear model (GLM) ANOVA and Tukey post hoc tests, when applicable. Because baseline and every fourth week program data will be available after the completion of the first 12 weeks the effect of training on CRF (VO_2_max) and cardiometabolic measurements (TC, HDL, LDL, resting BP, and resting HR) will be determined using repeated-measures GLM-ANOVA with the exercise intensity (individualized or standardized) as the between subjects factor. Between group 12-week changes will be analyzed using GLM-ANOVA and Tukey post hoc tests, when appropriate. The assumption of normality will be tested by examining normal plots of the residuals in ANOVA models and will be regarded as normally distributed if Shapiro-Wilk tests are not significant [12]. Effect sizes will be calculated using means and pooled standard deviations. Method of data analysis will be analysis by treatment administered. Only participants who complete ≥ 70% exercise training sessions and strictly adhere to target exercise intensity will be included in the statistical analysis. The probability of making a type I error will be set at *p* ≤ 0.05 for all statistical analyses.

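### The four-visit repeated-measures ANOVA drops any eligible participant with one missed test; the loss is confined to the time-course analysis and a mixed model avoids it

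*Protocol article*

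**What the plan says.** Under Statistical analysis, Time course changes, the Protocol article states that the effect of training on VO2max and the cardiometabolic measures "will be determined using repeated-measures GLM-ANOVA", with the two training arms as the between-subjects factor. The visits come from the Testing section: "Testing sessions for both the experimental and control groups will be conducted at baseline and every fourth week during the 12-week intervention period". That makes four: baseline and weeks 4, 8 and 12. On software, the article says "All analyses will be performed using IBM SPSS Version 22.0", with GraphPad Prism named alongside. It describes neither imputation nor a likelihood-based method for a missed test.

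Three other provisions bear on the point:

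- The same section plans a separate GLM-ANOVA of between-group 12-week changes. The Incidence of response section plans a chi-squared test on the change from baseline to the end of the first 12 weeks.
- Both sections restrict the analysis to participants who attend at least 70% of sessions and keep strictly to the target intensity.
- The Sample size calculation section asks for 16 evaluable participants per group. It adds: "It is assumed there would be an approximate 20% dropout rate", and therefore aims for 20 per group.

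**The concern.** A repeated-measures GLM in SPSS takes one row per participant and deletes any row with a gap. Someone tested at baseline and at weeks 4 and 12 who misses week 8 leaves the model, and three observed values go with them.

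The analysis affected is not marginal. Research aims calls the time-course comparison between arms a key secondary aim, and this is the only planned analysis that uses weeks 4 and 8. Missed tests are plausible: each visit asks for a 12-hour fast, a maximal test and a verification bout, and a participant who does not reach VO2max has to come back on another day. At 16 to 20 per arm, losing even two or three people per arm is noticeable.

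**Working it through.** **1. The plan's own figure.** Inflating 16 evaluable participants for 20% dropout gives 16 / (1 − 0.20) = 20 per group, as stated. Week-12 values that are absent because of dropout are therefore already allowed for. (How 16 was obtained from the effect size is a separate matter and is not used here.)

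**2. Loss from intermittent misses.** Take the 16 per arm who have a week-12 test. Let *m* be the chance of missing each of the week-4 and week-8 tests, independently. The documents give no value for *m*, so a range is shown.

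- Kept by the four-visit model: 16 × (1 − *m*)²
- SE multiplier for the arm contrast, against all 16: 1 / √[(1 − *m*)²] = 1 / (1 − *m*)

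| *m* (assumed) | Kept per arm | Observed week-12 values unused in this model | Rise in SE |
|---|---|---|---|
| 0% | 16.0 | 0 | 0% |
| 2% | 15.4 | 0.6 | 2% |
| 5% | 14.4 | 1.6 | 5% |
| 10% | 13.0 | 3.0 | 11% |
| 15% | 11.6 | 4.4 | 18% |

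**3. Adding dropout.** Assume 20 recruited per arm, 20% dropout spread evenly over the three intervals, within-person correlation of 0.6 to 0.9 (compound symmetry or AR(1)) and known covariance. Compare the SE of the week-12 minus baseline arm contrast from complete cases with that from a mixed model on all available visits.

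- Dropout only, *m* = 0: complete-case SE is 2–5% larger. At correlation 0.8, in units of the SD, it is 0.224 against 0.218 under compound symmetry and 0.349 against 0.333 under AR(1).
- *m* = 5%: 8–11% larger.
- *m* = 10%: 14–17% larger.

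**4. What the attendance rule already removes.** Three sessions a week for 12 weeks is 36 sessions. A participant who stops at week 8 has at most 24/36 = 67%, below 70%. The threshold is 0.70 × 36 = 25.2, so 26 sessions, reached only in week 9. Most dropouts are thus excluded whatever the model, and the 2–5% in step 3 overstates what a change of model alone recovers.

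**5. The other analyses.** The 12-week change needs only baseline and week 12, so in step 2 it keeps all 16. The calculation shows the same with 20 per arm, no dropout, *m* = 5% and AR(1) correlation 0.6. The SE is 0.417 from four-visit complete cases. It is 0.396 from both the mixed model and the simple 12-week change. The loss belongs to the four-visit model alone.

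**The case against.** The strongest reply is that the planned week-12 analyses keep the week-12 data. A reader might infer that the trial discards observed week-12 values generally. It does not: the 12-week-change GLM-ANOVA and the responder test both retain a participant who missed only week 4 or week 8. This stands, and it limits the point to the time-course model.

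It also affects how the gain is sized. Suppose each of the three follow-up tests is missed with probability 5%, 10% or 15%, with assumed SDs of 20 (between person), 5 (individual response) and 4 (test error), in percent of baseline. A mixed model then has 0.87, 0.76 or 0.65 of the variance of the four-visit complete-case analysis for the baseline-adjusted week-12 contrast. Against an analysis that keeps every week-12 value, those ratios are divided by (1 − *m*)²: 0.87/0.9025 = 0.96, 0.76/0.81 = 0.94 and 0.65/0.7225 = 0.90. On week 12 itself the gain is therefore 4–10% of the variance, not 13–35%.

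It can also be said that few intermittent misses should occur, because the week-4 and week-8 tests set the exercise prescription and a test in which VO2max is not reached is to be repeated. That is reasonable. It is why the result is given as a range that includes zero.

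Finally, a condensed article may leave missing-visit handling and sphericity corrections to a plan not shown here. That is fair for those details, and treating baseline as a level of the repeated factor is a standard design and not an error. But the model itself is named in the article, so its choice can be judged.

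**Conclusion.** The point holds in limited form, as an inexpensive improvement to the time-course analysis. Listwise deletion there brings the usable number below the planned 16 per arm as soon as some tests are missed at weeks 4 or 8. At an assumed 5–10% per visit, about 1.6 to 3.0 completers per arm are lost and the SE in that model rises by about 5–11%. With no intermittent misses, no observed week-12 value is lost and only dropouts' earlier visits are wasted.

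Two stronger readings are not supported. The first is that the 20% dropout measures the loss: a dropout has no week-12 value to discard, and the inflation from 16 to 20 already covers it. The second is that the model choice biases the arm comparison. Complete-case selection could do so if missed tests relate to response, but nothing in the article shows that they do. Selection after randomisation comes mainly from the attendance and adherence rule, which a change of model would leave in place.

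The sizes rest on assumed missing rates, independence between visits and, for the dropout figures, an assumed correlation structure.

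**What to change.** Within the analysis set the protocol uses, replace the repeated-measures GLM-ANOVA with a linear mixed model for the values at weeks 4, 8 and 12:

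- fixed effects for arm, visit and arm-by-visit, with the baseline value as covariate;
- unstructured within-person covariance and Satterthwaite degrees of freedom;
- all available follow-up tests, so that one missed visit no longer removes the participant.

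Take the time-course contrasts and the week-12 contrast from this one model. The same outcome is then not analysed on two different sets of participants. The model assumes data missing at random given baseline and the observed visits, which is weaker than what complete cases generally need. As a side benefit it does not require sphericity.

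The cost is a change of analysis wording. The named software can fit the model, and no visit, test or recruitment target changes. Whether to replace the 70% attendance and adherence restriction is a separate question. Including every randomised participant would change the analysis population and should be decided on its own merits.

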### Sample – control group

Due to moral and ethical issues related to excluding participants from an exercise intervention to improve health, a control group will be recruited as a separate cohort. The control group participants must meet the same inclusion criteria and will not be allowed in the study if they meet the exclusion criteria, as previously mentioned.

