#### Exercise intervention

After the completion of the baseline testing, participants will be randomly allocated to either the individualized or standardized arms at a 1:1 ratio using a computerized stratified minimization sequence. One of the primary investigators will have knowledge of the treatment groups to which participants have been allocated in order to interpret test results and prescribe target exercise intensities. However, this same investigator will not be involved in the implementation of the exercise training programs (to be completed by research assistants) in order to mitigate researcher bias. Participants will then be asked to come to the laboratory on Monday, Wednesday, and Friday to take part in the community wellness program and subsequent research. Upon arrival each day, participants will be asked to rest comfortably for 5 minutes in the seated position. Then, their resting BP and HR will be recorded. Following the resting measurements, participants will complete a 5-minute warm-up starting at a low and progressively increasing intensity until they are ready to begin their CRF exercise session. At this point, participants will be asked to stay within the designated HR (described in further detail below) outlined on their exercise log as determined based on their experimental group and week of experimental trial. At approximately 1/3 and 2/3 the total session time, an exercise physiologist or research assistant will record their current HR, rating of perceived exertion (scale 1–10), intensity of aerobic equipment, and any other pertinent notes. At the end of the CRF exercise session, the participant will be asked to complete a cooldown in which the exercise intensity is gradually reduced. While resistance training is not part of this proposed experiment, it is an integral part of the community wellness program and could be a confounding factor to the overall incidence of response. Therefore, all participants will be asked to complete the resistance training after the CRF training session is completed in order to have consistency among all participants. During the first 4 weeks, there will be no resistance training. During the next 4 weeks (week 4–8), there will be a learning and anatomical adaptation phase to resistance training in which proper technique and range of motion will be emphasized and participants will be acclimated to the resistance training machines. During the last 4 weeks (week 8–12) participants will complete one set of 8–12 repetitions on eight machine-based resistance training exercises and progress to two sets by the end of the 12th week [19].

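### The between-group test of 12-week change names no baseline covariate, and its Tukey step implies that the non-randomised control cohort shares a comparison family with the randomised contrast

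*Protocol article*

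**What the plan says.** All references are to the protocol article.

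- **Test of 12-week change** (Statistical analysis, Time course changes): "Between group 12-week changes will be analyzed using GLM-ANOVA and Tukey post hoc tests, when appropriate". The sentence names no covariate and does not list the groups.
- **Baseline** (same section): "Baseline-dependent variables will be compared using general linear model (GLM) ANOVA and Tukey post hoc tests, when applicable". Nothing says that this comparison leads to an adjustment.
- **Companion test** (same section): a repeated-measures ANOVA over baseline and the four-weekly visits. Its between-subjects factor has two levels, individualised and standardised.
- **Error rate** (same section): "The probability of making a type I error will be set at *p* ≤ 0.05 for all statistical analyses". Sidedness is not given.
- **Allocation** (Exercise intervention): only the two exercise arms are randomised, 1:1, "using a computerized stratified minimization sequence". The factors are not named.
- **Controls** (Sample – control group): "a control group will be recruited as a separate cohort". Table 2 gives the 12-week changes as the only analysis for this group.
- **Incidence of response**: a chi-squared test compares responders between the two exercise arms.

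**The concern.** Individualised versus standardised is the only randomised contrast, and it rests on about 16 evaluable participants per arm. Two features of the stated test may cost it precision.

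First, a change score fixes the slope on baseline at 1. Wherever the true slope is below 1, part of any chance baseline difference stays in the estimate as noise that a baseline-adjusted model would remove.

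Second, a Tukey procedure protects all pairwise comparisons among the groups. If the controls are one of those groups, the randomised contrast meets a stricter threshold in order to protect two comparisons with a cohort that was never randomised.

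Baseline values are collected for everyone, so neither loss is needed.

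**Working it through.** **Inputs.** From the Sample size calculation: 16 evaluable per group; "Assuming a power of 0.80 was needed"; "the calculated effect size for change in VO_2_max was 0.30". The 20% dropout allowance reproduces: 16/(1 − 0.20) = 20. The metric of the 0.30 is not stated and no SD is given ("The means and standard deviations of a previous study [5] were examined"), so everything below is in units of the SD of change.

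**Assumptions.** Two-sided 0.05; 16 in each of three groups where controls are included; baseline-to-week-12 correlation ρ not in the document, so shown as a range; standardised difference d shown as a range. The value d = 1.02 is not the protocol's. It is the difference at which a two-arm t test with 16 per arm has 80% power, and so serves as a reference point. Read as d, the protocol's 0.30 gives very low power by either route. How 0.30 leads to 16 per group is a separate question.

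**1. Is a third group implied?** With two groups, Tukey is identical to the t test (critical value 2.042 and power 80.0% for both). It matters only with three or more groups, and the control cohort is the only third group. The repeated-measures ANOVA and the chi-squared test name only the exercise arms, so the change ANOVA is the one outcome test described that the controls could enter. Table 2 fits this. The inference is strong, but the protocol does not state it.

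**2. Cost of Tukey on that reading.**

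- Two-arm critical t: 2.042 (30 df).
- Tukey, three groups: studentized-range quantile/√2 = 2.424 (45 df), a per-comparison level of about 0.0195.
- 95% half-width: 2.042 × √(2/16) = 0.722; 2.424 × √(2/16) = 0.857. Ratio 0.857/0.722 = 1.19.

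| Assumed d | n per group | Two-arm test | One of three Tukey pairs |
|---|---|---|---|
| 0.30 | 16 | 13.0% | 6.6% |
| 0.80 | 16 | 59.1% | 44.3% |
| 1.02 | 16 | 80.0% | 68.1% |
| 1.02 | 20 | 88.4% | 79.4% |

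At d = 1.02, Tukey needs 21 per group for 80% power. Having the controls in the error term does no harm: without Tukey, their extra degrees of freedom move power from 80.0% to 80.9%. The loss comes from the multiplicity adjustment alone.

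**3. Cost of leaving baseline out.** With equal variances σ² at both visits:

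- variance of the change-score contrast: 2σ²(1 − ρ) × 2/n
- variance of the ANCOVA contrast: σ²(1 − ρ²) × 2/n
- ratio: (1 + ρ)/2

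| Assumed ρ | Variance ratio | Equivalent n per arm (16/ratio) | ANCOVA power at d = 1.02 (change score 80.0%) |
|---|---|---|---|
| 0.5 | 0.75 | 21.3 | 88.8% |
| 0.7 | 0.85 | 18.8 | 84.7% |
| 0.8 | 0.90 | 17.8 | 82.6% |
| 0.9 | 0.95 | 16.8 | 80.6% |
| 0.95 | 0.975 | 16.4 | 79.5% |

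The power column allows for the degree of freedom spent on the covariate. Simulation (20,000 trials per setting) agrees: 80.1% against 84.7% at ρ = 0.7, and 79.8% against 80.6% at ρ = 0.9.

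**4. Does the companion test supply the adjustment?** No. The repeated-measures ANOVA treats baseline as one of the outcome occasions. Its group effect averages in a pre-treatment value, and its interaction is an omnibus test over four occasions. Neither conditions on baseline.

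**The case against.** The strongest objection is that the Tukey penalty is inferred. The change ANOVA does not list its groups, and the Tukey step applies only where appropriate. A reader might infer that the trial's primary contrast is tested at about 0.0195. The document does not support that: the same contrast is also tested at 0.05, without Tukey, in the two-arm repeated-measures ANOVA and in the chi-squared test. The latter addresses the main aim, incidence of non-response. This objection stands, so the power loss is conditional and belongs to this one test.

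A reader might also infer that baseline is ignored or the estimate biased. Neither follows. A change score subtracts baseline, and under randomisation its contrast is unbiased. What is lost is efficiency, and the amount depends on a correlation the document does not give. A 30–75 age range and verified VO2max make a high correlation plausible, and there the gain nearly disappears.

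It is tempting to add that omitting the minimisation factors makes the standard error too large. That cannot be shown: the factors are not named, so neither their prognostic strength nor the cost of omitting them is known. If baseline fitness is one of them, chance imbalance in it is already limited.

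It could be said that an article leaves covariates to a fuller plan. This does not dispose of the point. The article does state a method for the between-group change, and a better one is available from data already collected.

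**Conclusion.** The point holds as a recommendation to improve a stated analysis; it does not show an invalid test. Two parts differ in strength.

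- **Certain from the text:** the change ANOVA names no baseline term and the repeated-measures model does not supply one. The precision forgone is 25%, 15% or 5% of the variance at assumed ρ of 0.5, 0.7 or 0.9, under equal variances. At ρ = 0.95 there is no power to gain.
- **Strongly implied but not written:** the controls join the Tukey family. If so, with 16 per group, power on the randomised contrast in this test drops by about 12 points at d = 1.02 and about 15 at d = 0.8. Both values of d are assumed. If the ANOVA holds only the two exercise arms, Tukey costs nothing.

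**What to change.** Replace the sentence on between-group 12-week change with the following:

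- For VO2max, fit a linear model of the week-12 value on arm and baseline value, adding the factors used in the minimisation. Use the same form for lipids, blood pressure and heart rate.
- Name individualised versus standardised as the single contrast, at two-sided 0.05, outside any Tukey family.
- Report comparisons with the control cohort separately, labelled as a non-randomised reference.

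This is a change of wording. It needs no new data, and the planned software can fit the model. The downside is a few degrees of freedom out of about 32 evaluable participants in the two arms, with negligible gain if the pre-post correlation proves very high.

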#### Incidence of response

Delta values (Δ) will be calculated (post-testing minus baseline value divided by baseline value) for percent change in relative VO_2_max, TC, HDL, LDL, resting BP and resting HR and participants will be categorized as: ‘1’ = responder (% Δ > TE) or ‘0’ = non-responder (% Δ ≤ TE). Chi-squared (*χ*
^2^) tests will be subsequently used to analyze the point prevalence of responders and non-responders to exercise training separated by exercise intensity group (individualized and standardized) between baseline and the end of the end the first 12-week intervention. Only participants who complete ≥ 70% exercise training sessions and strictly adhere to target exercise intensity will be included in the statistical analysis. The probability of making a type I error will be set at *p* ≤ 0.05 for all statistical analyses.

In order to make inferences about the true values (population values) of the effect of both exercise interventions on VO_2_max and cardiometabolic factors, the uncertainty in effect will be expressed as 90% confidence limits and the likelihood the true value of the effect represents a substantial and clinically meaningful change (harm or benefit). Effects will be declared unclear if the confidence interval overlapped thresholds for substantiveness or the effect could be substantially positive and negative or beneficial and detrimental. All probabilistic magnitude-based inferences will be calculated using a published spreadsheet [27].

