### Research aims

The objective of this research is to determine the incidence of response to VO_2_max after implementation of a standardized (%HRR) and individualized (based on first ventilatory threshold [VT1] and second ventilatory threshold [VT2]) approach to exercise prescription in a community wellness program for 12 weeks. The primary measurement outcome will be VO_2_max with secondary outcomes of total cholesterol (TC), high-density lipoprotein (HDL), low-density lipoprotein (LDL), triglycerides, blood glucose, and resting heart rate (HR) and blood pressure (BP). Thus, the main research aim is to determine whether an individualized exercise prescription decreases the incidence of non-response to CRF and cardiometabolic measurements compared to the standardized approach. Similarly, another primary research aim is to determine if changing the prescription of CRF intensity for a subsequent 12-week intervention elicits more responsiveness in previously categorized non-responders (based on VO_2_max responses). A key secondary aim of this research is to establish whether there are differences in the time course changes of VO_2_max and cardiometabolic risk factors between the experimental groups every fourth week during the 12-week intervention.

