Testing will be conducted in a university-based performance laboratory under the supervision of three exercise physiologists. Prior to completing the testing sessions, participants will be asked to refrain from food and drink (other than water) for 12 hours prior to the testing session, be well hydrated prior, avoid the use of alcohol, caffeine, and tobacco within 24 hours of testing, be well rested, avoid significant exertion or exercise the day of testing, and report any medication use prior to testing. Testing will occur as close to the same time of day as possible with the above directions prior to each testing session. Following the blood lipid profile testing (explained in detail later) and prior to the maximal exercise test, participants will be provided a small snack. The testing will be conducted as follows:Dietary analysis: participants will be instructed to not change their usual diets throughout the study and asked to complete a 3-day dietary intake recall including two weekdays and one weekend day to evaluate energy intake and the proportion of kilocalories from carbohydrates, protein, and fat.Anthropometric measurements: participants will be weighed on a calibrated, medical-grade scale to the nearest 0.01 kg and height will be measured using a stadiometer to the nearest 0.5 cm. Waist circumference will be measured by the narrowest horizontal circumference above the umbilicus and below the xiphoid process to the nearest 0.5 cm [4].Resting heart rate (RHR) and BP measurements: procedures for RHR and BP will follow standard guidelines [4]. In summary, participants will be required to sit for 5 minutes with sufficient back support, feet on the ground, and arms supported at heart level. Resting heart rate will be recorded by using a medical-grade pulse oximeter after the 5 minutes of seated rest. Blood pressure will be measured using a stethoscope and sphygmomanometer to determine left arm brachial artery BP on consecutive measure separated by 1 minute. The mean of the systolic and diastolic measures will be considered the resting BP.Fasting blood glucose and lipid measurements: all fasting lipid and blood glucose measurements will be analyzed using the Cholestech LDX system (Alere, Waltham, MA, USA), which has been shown to have excellent reproducibility [13, 14]. An optics check of the Cholestech LDX system will be completed at the beginning of each testing session. Participants will be asked to thoroughly wash hands with soap and rinse with warm water. The skin will then be wiped with an alcohol swab and allowed to dry. Using a lancet, the distal end of the third digit of the right hand will be punctured and a finger stick sample will be collected using a 40 μl capillary tube with blood flowing freely into the tube without milking the finger. The blood sample will then be extracted into a commercially available test cassette for analysis. Measurements of TC, HDL, LDL, triglycerides, and blood glucose will be obtained. Upon completion of the blood profile testing and data collection, blood samples will be disposed of based on standard biohazard procedures.VO_2_max and verification bout: participants will complete a modified Balke, pseudo-ramp graded exercise test (GXT) on a power treadmill. Participants will walk or jog at a self-selected pace with an increase in incline of 1% every minute until volitional fatigue. Heart rate and expired gas will be measured continuously using a heart rate monitor and a calibrated metabolic analyzer, respectively. Data will be analyzed following guidelines previously reported [5]. In summary, gas exchange data will be time averaged for every 15 seconds, VO_2_max will be determined by averaging the last two 15 second samples, and maximal HR will be the highest achieved HR during the GXT.

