#### Categorizing responders and non-responders

Following the 12-week intervention, the participants will be categorized as responders and non-responders (see statistical analysis section for further details) for each testing measurement. While each testing measurement will be evaluated, the overreaching categorization of responder and non-responder will be based on VO_2_max due to the profound health and performance implications of this measurement.

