#### Biological variability

Intraclass correlation (ICC) of variation, typical error and co-efficient of variation (CV) for VO_2_max, resting HR, resting BP, and fasting blood glucose, total cholesterol, HDL, and LDL will be calculated as described previously [26]. The CV will be combined with the measurement error of the testing to determine the TE. The TE will be used to categorize responders and non-responders. In summary, for all criteria tested the changes in pre- to post- intervention will be analyzed with responders having a change > TE and non-responders having a change that is ≤ TE.

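### Triglycerides and blood glucose are declared secondary outcomes but are missing from the listed time-course and responder analyses, and triglycerides have no technical error

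*Protocol article*

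**What the plan says.** **Declared.** Research aims names "secondary outcomes of total cholesterol (TC), high-density lipoprotein (HDL), low-density lipoprotein (LDL), triglycerides, blood glucose, and resting heart rate (HR) and blood pressure (BP") alongside the primary outcome, VO2max. The same section makes non-response in fitness and cardiometabolic measures the main aim, and differences in their time course a key secondary aim.

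**Measured.** Under Testing: "Measurements of TC, HDL, LDL, triglycerides, and blood glucose will be obtained". On timing: "Testing sessions for both the experimental and control groups will be conducted at baseline and every fourth week during the 12-week intervention period". Tables 1 and 2 mark triglycerides and blood glucose at baseline and weeks 4, 8 and 12, for the experimental and control groups.

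**General rules.** Categorizing responders and non-responders has participants classified "for each testing measurement". Biological variability applies the threshold rule to all criteria that are tested.

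**Explicit lists.**
- Biological variability (reliability statistics and TE): VO2max, resting HR, resting BP, "and fasting blood glucose, total cholesterol, HDL, and LDL will be calculated".
- Time course changes (repeated-measures model): VO2max and "cardiometabolic measurements (TC, HDL, LDL, resting BP, and resting HR").
- Incidence of response (responder classification and chi-squared test): "percent change in relative VO_2_max, TC, HDL, LDL, resting BP and resting HR".

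**Analyses without a list.** Time course changes also plans a between-group comparison of 12-week changes. Incidence of response plans 90% confidence limits and magnitude-based inference for cardiometabolic factors in general.

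**The concern.** The article does not leave the choice of analysed outcomes to a later document. It names them in three places, and the names do not match the declared outcomes, the general rules or one another. Glucose is in the TE list but in neither analysis list; triglycerides are in none of the three.

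A reader cannot tell whether this is a slip or a deliberate exclusion. Whoever analyses the trial could follow the lists and omit both outcomes, or follow the general rules and report them, and could defend either choice from the text. That choice should not remain open once results are visible. For triglycerides there is a further risk: a TE derived after the data are known could be set with knowledge of whom it makes a responder.

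**Working it through.** No stated figure is at issue, so the check compares lists. The declared outcomes come from Research aims, the visits from Tables 1 and 2, and the remaining columns from the three statistical subsections.

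| Declared secondary outcome | In TE list | In repeated-measures list | In responder list |
|---|---|---|---|
| Total cholesterol | yes | yes | yes |
| HDL | yes | yes | yes |
| LDL | yes | yes | yes |
| Resting HR | yes | yes | yes |
| Resting BP | yes | yes | yes |
| Blood glucose | yes | **no** | **no** |
| Triglycerides | **no** | **no** | **no** |

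**Counts.** There are 7 declared outcomes. The TE list omits 7 − 6 = 1 (triglycerides). The repeated-measures and responder lists each omit 7 − 5 = 2 (triglycerides and glucose). The share missing from both analyses is 2/7 = 29% with blood pressure counted once, or 2/8 = 25% with systolic and diastolic counted separately. This is a count of items; it does not measure bias or power.

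**What can still be done with each outcome as the text stands:**

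1. *Glucose, responder status.* Data, a TE and a general rule that covers all tested criteria all exist. It can be classified, although the responder list does not name it.
2. *Triglycerides, responder status.* The rule compares the change with the TE, and no triglyceride TE is planned. It cannot be derived as written. The data to derive it will exist: Biological variability and technical error has 15 participants complete the baseline assessments twice within two weeks, and the finger-stick sample in that battery yields triglycerides.
3. *Both, time course.* Four-visit data exist and the planned model could be applied unchanged, but the list does not call for it.
4. *Both, 12-week change and magnitude-based inference.* Neither analysis carries a restricting list, so both outcomes can be included.

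**Direction of response.** Incidence of response defines Δ as (post − baseline)/baseline and a responder as % Δ > TE. Suppose a TE of 10% (an assumed value for illustration). A fall from 100 to 80 gives Δ = (80 − 100)/100 = −20%, which is not above 10%, so the participant is a non-responder. A rise from 100 to 120 gives Δ = +20% and the participant is a responder. Adding the two names to the list without stating a direction would therefore score an increase in triglycerides or glucose as a response. The Discussion refers to improvement in a positive direction only when it describes two earlier studies.

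**The case against.** The strongest reply is that the general rules already cover both outcomes. Every testing measurement is to be categorised, the threshold rule applies to all tested criteria, and two of the planned analyses have no list. Nothing says that the named variables are the only ones to be analysed. Both outcomes are publicly declared and scheduled, so dropping them from the report would be noticed. The omission of triglycerides may be no more than a word lost from a list, and the retest data to repair it will be collected anyway.

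Much of this stands. A reader might infer from the lists that two secondary outcomes cannot be answered at all, that the glucose TE is never used, or that the main aim fails for these measures. The documents do not support any of these: glucose has a threshold and a rule, and both outcomes have data and unlisted analyses open to them. Nor do the documents show any intention to report selectively; they only leave room for it.

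Two things remain. The sentence promising categorisation of every measurement sends the reader to the statistical analysis section for the details, and that section's lists leave the two outcomes out, with no wording to mark those lists as examples. And even on the most generous reading, triglycerides have no planned threshold. The unlisted analyses also do not replace the responder comparison, which serves the main aim, or the repeated-measures test, which serves the key secondary aim.

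**Conclusion.** The point holds as an internal contradiction of limited reach. Two of seven declared secondary outcomes, measured at all four first-stage visits, are missing from the explicit lists of both the repeated-measures and the responder analyses. One of the seven, triglycerides, is also missing from the TE list, and its responder status cannot be derived as written. For glucose, and for the time course of both outcomes, the text is inconsistent but the analysis is feasible.

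VO2max as the primary outcome, the VO2max-based entry to the second 12 weeks, and the sample size, which was set on change in VO2max, are untouched.

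The conclusion assumes that the three lists are meant to state what will be analysed. If they were meant as examples, the remaining defects are the missing triglyceride TE and the unstated direction of response. The correction should be made before data are seen.

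**What to change.** 1. In Biological variability, add triglycerides to the variables for which the ICC, typical error and CV are calculated, using the repeat baseline tests of the 15 retest participants, and combine the CV with measurement error as for the other variables.
2. In Time course changes and Incidence of response, add triglycerides and blood glucose to the outcome lists.
3. In Incidence of response, state that for these two outcomes a response is a decrease larger than the TE, that is % Δ < −TE. It would be sensible in the same sentence to state the direction for every outcome already listed.
4. If the omission was intended, remove the two explicitly as secondary outcomes instead, and make the general categorisation rules agree.

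Either route should be dated before data are seen. The cost is a few sentences of text. The blood samples, visits and retest data are already planned, so no measurement or participant is added.
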